### Recruitment {15}

Each of the ten participating pediatric university clinics is responsible for recruiting its own participants. The recruitment period is 24 months. Prior to the recruitment, each clinic provided the project management team their average number of patients per month. On average, we expect 160 patients to be recruited in 24 months in each clinic. If recruitment difficulties arise, the recruitment period might be extended.

## Assignment of interventions: allocation

### Sequence generation {16a}

The cluster-randomized controlled, multicenter study encompasses ten participating pediatric university clinics, equally divided into five intervention and five control centers. The cluster-randomization was conducted centrally by the Institute of Medical Biometry and Statistics, University of Lübeck. We used a covariate-constrained cluster-randomization as implemented in R (package cvcrand, version 0.1). The variables experience of the center and number of expected families recruited per month were used as covariates.

### Concealment mechanism {16b}

The study site allocation was delayed as long as possible to ensure that sites had signed agreements and contracts to participate: final study sites had been identified, ethics approval obtained, and the study launch confirmed.

### Implementation {16c}

The result of the cluster-randomization was communicated to all participating pediatric university clinics in March 2023. All families within one center will receive the same intervention. To ensure commitment to the study, the cluster-randomization result was disclosed only after obtaining either a bilaterally signed collaboration agreement or a letter of intent from the participating clinics, regardless of the randomization outcome.

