### Who will take informed consent? {26a}

Study nurses and physicians at the participating pediatric university clinics will identify and approach potential participants. Ample time will be provided to individuals to contemplate their participation and voluntarily decide to join the study. Prior to participation, parental/caregiver consent will be obtained through a digital informed consent (“opt-in”). Moreover, all patients aged 16 years and older will also undergo a digital informed consent process.

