## Intervention description {11a}

### Screening

A local study nurse will screen potential participants in the intervention and control groups based on predefined criteria (see the “Eligibility criteria {10}” section). Eligible individuals will be contacted by mail or phone, providing detailed study information. Prior to participating, all individuals will give informed consent during the clinic’s waiting time before their long-term follow-up appointment.

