### Plans to promote participant retention and complete follow-up {18b}

Participation in the intervention requires attending a counseling session with a member of the psychosocial team. Subsequent counseling appointments are optional and can be conducted either in person at the clinic or through online meetings, providing flexibility and increasing the likelihood of continued participation. To ensure the likelihood of complete follow-ups, participants receive a voucher of EUR 25 when they complete all follow-ups. Additionally, they receive up to two reminders via telephone and email if they do not respond within two weeks.

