### Methods in analysis to handle protocol non-adherence and any statistical methods to handle missing data {20c}

If a participant declines study participation, the attending physician notes baseline data (age, gender, cancer diagnosis, and reason for declining participation) in a list and sends the consented baseline data to Lübeck every month. For missing values in the follow-up assessments, we will conduct multiple imputations.

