## Trial status

The trial is registered on the German Clinical Trials Register (https://www.drks.de/DRKS00029269) with the registration number DRKS00029269. The current protocol is version 1.0 of 1 June 2023. The recruitment started on 1 July 2023. The approximate date of recruitment completion is 30 April 2025.

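### Clinic staff know their arm before recruiting any family, and only the intervention arm carries a counselling condition, so the arms can differ in who is enrolled and analysed

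*Protocol article*

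**What the plan says.** All of this comes from the protocol article.

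- **Disclosure of allocation.** Implementation {16c}: "The result of the cluster-randomization was communicated to all participating pediatric university clinics in March 2023". The same section adds: "All families within one center will receive the same intervention". A clinic that knows its own arm therefore knows the arm of every family it will see.
- **Start of recruitment.** Trial status: "The recruitment started on 1 July 2023".
- **Who recruits.** Section {26a}: "Study nurses and physicians at the participating pediatric university clinics will identify and approach potential participants". Screening: "A local study nurse will screen potential participants in the intervention and control groups based on predefined criteria", and then "Eligible individuals will be contacted by mail or phone, providing detailed study information". Consent follows in the waiting room. The baseline survey (T0), which includes the primary outcome, is completed there on a tablet before the appointment (Plans for assessment {18a}).
- **Concealment and blinding.** Concealment mechanism {16b} and Implementation {16c} describe holding back the result until sites had committed themselves. Section {17a} says that patients and parents cannot be blinded and that analysts will be. It does not mention recruiting staff.
- **Counselling condition.** Section {18b}: "Participation in the intervention requires attending a counseling session with a member of the psychosocial team". Later sessions are optional. The eligibility criteria {10} do not mention counselling. The Psychosocial support section lets individual need decide the number of contacts.
- **Analysis set.** Section {20a} confines the full analysis set to participants who began the intervention. Section {20b} treats intention-to-treat as a separate population for sensitivity analyses.
- **Decliners.** Under {20c} the physician lists age, gender, diagnosis and reason for each refusal, and "sends the consented baseline data to Lübeck every month".

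**The concern.** Randomizing clinics makes the clinics comparable in expectation. It does this for families only if the way families enter is unaffected by the arm. Here each step from identification to T0 is carried out by people who know the arm. A recruiter with a programme to offer may approach, or persuade, different families from a recruiter who offers only questionnaires.

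The counselling condition could add to this. In an intervention clinic, a family that does not want counselling has a reason to decline or not to begin. In a control clinic it has no such reason. Willingness to be counselled could plausibly be related to self-efficacy or to how it changes, and self-efficacy is an unblinded self-report. A difference at two or three months could then partly reflect who is in each arm rather than what the programme did.

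**Working it through.** **1. Sequence.** Clinics learned their arm in March 2023 and recruitment opened on 1 July 2023, three to four months later. No family can have been identified, invited, consented or measured before its clinic knew the arm. No independent or blinded recruiter is described.

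**2. Two routes to loss in one arm only.**

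- *Before enrolment.* The {18b} condition, if presented at invitation, can deter families in intervention clinics only.
- *After enrolment.* A family may enrol and then refuse counselling. Section {18b} read together with {20a} leaves open whether it began the intervention and so belongs in the primary analysis. The intervention also has a medical part, so the answer is not fixed by the text. Controls face no comparable test.

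**3. What the safeguards reach.**

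- Predefined screening criteria settle who is eligible, not who is actually approached or how.
- The decliner list records the reason for refusal, which is useful. It holds no self-efficacy score, forwards only consented data, and does not cover families never approached.
- Covariate adjustment {20a} works for measured traits. T0 is itself taken after the clinic's arm is known, and adjusting for it does not remove a difference in expected change.
- Monitoring of screening {23} checks quality and reliability. It does not hide the arm.
- The constrained randomization {16a} balanced two clinic-level variables only.
- The intention-to-treat sensitivity analysis {20b} could recover families on the second route but not on the first.

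**4. Size, by assumption.** The plan gives no participation rates, so there is no figure of its own to reproduce. Suppose a share p of eligible families is lost from one arm only, and these families differ from the rest by d SD in expected change in self-efficacy. The mean of that arm then shifts by p × d.

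- Low: 0.20 × 0.3 = 0.06 SD, and 0.06 / 0.3 = 20% of the planned effect.
- High: 0.30 × 0.5 = 0.15 SD, and 0.15 / 0.3 = 50% of the planned effect.

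This supposes that all such families are lost in one arm and none in the other, so for given p and d it is a ceiling.

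**5. Effect on the test.** Inputs from the plan: ICC 0.022, 10% loss, alpha 0.05 (two-sided assumed), five clinics per arm. Equal clinic sizes are assumed. Sample size {14} gives at least 160 participants in total, while Recruitment {15} expects 160 per clinic. That mismatch is a separate matter, so both readings are shown. With m analysed per clinic, the design effect is 1 + (m − 1) × 0.022 and SE = √(2 × design effect / (5m)).

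- 160 per clinic: m = 144, design effect 4.146, SE = √(8.292/720) = 0.107 SD.
- 160 in total: m = 14.4, design effect 1.295, SE = √(2.590/72) = 0.190 SD.

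False-positive rate with no true effect (normal / t with 8 df):

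| Residual shift (SD) | m = 144 | m = 14.4 |
|---|---|---|
| 0 | 5% / 5% | 5% / 5% |
| 0.05 | 7.5% / 7.0% | 5.8% / 5.6% |
| 0.10 | 15.4% / 13.1% | 8.2% / 7.5% |
| 0.15 | 28.7% / 23.5% | 12.4% / 10.8% |

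The shift could also run against the programme. With m = 144, a true effect of 0.3 reduced by 0.10 to 0.2 would be detected about 46% of the time instead of about 80% (normal). More recruitment narrows the SE but leaves the shift unchanged.

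**The case against.** The strongest reply is that the plan shows an opportunity for bias and nothing more. A reader might infer that the intervention arm is in fact enriched with motivated families. No section reports any difference between arms, and even the direction is open, since families who want counselling could have lower self-efficacy. That objection stands.

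A reader might also infer that refusing counselling bars a family from the study. The text does not say so. Section {18b} speaks of taking part in the intervention, the eligibility criteria do not list counselling, and T0 comes after consent and before the appointment in both arms. Nor does one required session followed by optional ones flatly contradict need-based frequency. This narrows the point to an ambiguity, but the ambiguity still matters because {20a} makes beginning the intervention the test for the primary analysis.

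The decliner list is not the only safeguard either. Predefined criteria, training and procedures for nurses in both arms {11c}, covariate adjustment and monitoring of screening all help. None conceals the arm from those who recruit, and none accounts for families never approached.

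Finally, clinics that deliver a programme must know their arm, the invitation may already be identical across arms, and nothing says that families learn their arm before T0. The full protocol might settle the last two. Staff knowledge cannot be undone, so the remedy has to limit and document its effect.

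**Conclusion.** The point holds as a risk of differential recruitment and differential analysis, not as a demonstrated bias. The order of events and the one-sided counselling condition are in the text. The size is not: 0.06–0.15 SD rests on an assumed 20–30% lost from one arm and an assumed difference of 0.3–0.5 SD, and is an upper limit for those values. Within that range a residual shift of 0.10 SD would roughly triple the false-positive rate if 160 families per clinic are recruited, and would raise it to about 8% if 160 are recruited in total. The existing safeguards reduce the risk without removing it. As written, the plan would leave it difficult to tell a programme effect from a difference in who took part.

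**What to change.** 1. **Clarify the condition.** Reword {18b} and reconcile it with the eligibility criteria {10}, the Psychosocial support section and the analysis set in {20a}. The text should say that counselling is offered after T0 and that declining it does not prevent enrolment, follow-up or inclusion in the primary analysis. This concerns study entry and analysis only, not how much counselling a family should receive.
2. **Extend the decliner list** in {20c} to a consecutive anonymous log of all eligible patients booked for follow-up: age band, sex, diagnosis group, approached or not, enrolled or not. Keep it as far as data protection allows, and build it from appointment lists where it has to be retrospective. Report enrolment rates and characteristics by arm.
3. **Where ethics approval permits,** use the same invitation wording in both arms and keep T0 before the clinic's offer is discussed. This is the more debatable step, because it alters the information given to families, and a change during recruitment would mix two processes.

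The cost is an amendment and a few log fields for nurses who already screen. Some intervention families in the analysis will have taken no counselling, which slightly dilutes the estimated effect. The third item also requires revised information material.

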## Assignment of interventions: blinding

### Who will be blinded {17a}

Given the nature of the intervention, blinding of the patients and their parents is not possible. The data analysts will be blinded during the analyses.

### Procedure for unblinding if needed {17b}

A procedure for unblinding is not needed.

## Data collection and management

### Plans for assessment and collection of outcomes {18a}

At the baseline assessment (T0), the primary and the secondary outcome parameters will be assessed in the waiting time before the appointment at the clinic. Additionally, in the baseline assessment (T0), sociodemographic parameters are assessed with standard items based on the German Health Interview and Examination Survey for Children and Adolescents (KiGGS) survey, which is a representative long-term study on the health of children, adolescents, and young adults in Germany, conducted by the Robert Koch Institute [26]. The data assessment takes place via a tablet.

After two months (T1) and after three months (T2), all families receive a mail with links to the follow-up assessment. To increase the follow-up compliance, all families who do not take part in the follow-up assessment within one week receive a reminder by telephone and email.

### Plans to promote participant retention and complete follow-up {18b}

Participation in the intervention requires attending a counseling session with a member of the psychosocial team. Subsequent counseling appointments are optional and can be conducted either in person at the clinic or through online meetings, providing flexibility and increasing the likelihood of continued participation. To ensure the likelihood of complete follow-ups, participants receive a voucher of EUR 25 when they complete all follow-ups. Additionally, they receive up to two reminders via telephone and email if they do not respond within two weeks.

### Data management {19}

The primary outcome parameter, secondary outcome parameters, and self-reported sociodemographic data of patients and parents will be collected within the clinic setting using a tablet-based survey conducted through LimeSurvey (https://www.limesurvey.org). Once the survey via LimeSurvey is completed, an automatic routing mechanism leads the family to the SoSci Survey (https://www.soscisurvey.de), where their contact information is recorded. Reminders for follow-up surveys are sent to parents via email. Furthermore, physicians and study nurses collect patient medical data using CentraXX. The data are regularly checked for plausibility and completeness by the project management team in Lübeck. The data are protected, and access to the data is only possible with personal access. This procedure was devised in collaboration with the data protection officer in Lübeck and synchronized with all 10 clinics.

### Confidentiality {27}

For the cluster-randomized part of the study, participants will be assigned a unique ID upon giving informed consent, and all collected data will be stored under this ID. The central database in Lübeck will house these data, accessible externally by all study partners through CentraXX. Paper-based documentation forms will be archived by the study clinic for each participant for 10 years, adhering to the medical records retention period. Electronically stored medical data will be archived following the epidemiological practices outlined by the German Working for Epidemiology (German Acronym DAE) in 2004 for a minimum of 10 years. Participants can withdraw from the study at any time without any disadvantages, and in such cases, no further data will be collected. However, data processing that occurred before withdrawal will remain, unless the participant specifically requests data deletion along with withdrawal. Data deletion is only possible for non-anonymized data.

### Plans for collection, laboratory evaluation, and storage of biological specimens for genetic or molecular analysis in this trial/future use {33}

Not applicable. No biological specimens will be collected.

## Statistical methods

### Statistical methods for primary and secondary outcomes {20a}

For the primary objective regarding the primary efficacy endpoint, the primary hypothesis will be tested using a permutation test adjusted for cluster-level and subject-level covariates in the full analysis set, comprised of all participants who started the intervention. Details will be specified in the statistical analysis plan. The results will be complemented by estimates of the treatment effect using an adequate model that takes intra-cluster correlation into account (e.g., a linear mixed model or generalized estimating equations). As secondary objectives, we use the same model approach in the full analysis set to analyze the differences in the secondary efficacy endpoints.

A sequential testing procedure will be used to maintain a family-wise type I error of 0.05 for primary and secondary endpoints. If the primary endpoint is statistically significant at alpha = 0.05, the secondary efficacy endpoints will be tested. Hence, positive results on secondary endpoints can be interpreted inferentially only if a treatment effect is shown on the primary endpoint (gate-keeping). For all tested secondary endpoints, the significance level will be adjusted for multiple testing. The preliminary analysis plan is available upon request. The comprehensive analysis plan is currently being written and will be accessible in the German Clinical Trials Register once completed (https://drks.de/search/en/trial/DRKS00029269).

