### Description of the intervention

After providing informed consent, participants in both the intervention group and control group will engage in a tablet-based survey to evaluate primary and secondary outcomes during the clinic’s waiting time.

Participants in the control group receive conventional TAU, while participants in the intervention group receive a structured multidisciplinary intervention. This includes risk-based medical care and additional psychosocial support within the clinic.

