### Methods for additional analyses (e.g., subgroup analyses) {20b}

Subgroup analyses will be specified in the statistical analysis plan and will include subgroups stratified by tumor recurrence and experience of other major diseases or life events during the course of the intervention. Sensitivity analyses of the primary endpoint will include variations in the handling of missing data. Furthermore, the primary endpoint will be evaluated in the intention-to-treat (ITT) and per-protocol (PP) populations. Further sensitivity analyses include the analysis of the secondary endpoints in the ITT and PP populations.

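### The primary analysis set is conditioned on having started the intervention, a post-randomisation event with no stated counterpart under usual care, so the confirmatory comparison can be biased

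*Protocol article*

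**What the plan says.** Under Statistical methods for primary and secondary outcomes {20a}, the primary hypothesis is tested "in the full analysis set, comprised of all participants who started the intervention". The secondary endpoints use that same set, and they are tested only if the primary test is significant at 0.05. Under Methods for additional analyses {20b}, "the primary endpoint will be evaluated in the intention-to-treat (ITT) and per-protocol (PP) populations", and the secondary endpoints are also analysed in those populations as sensitivity analyses. The authors therefore treat ITT as different from their full analysis set, and it is not the primary set.

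Four other sections bear on what starting means:

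- **Description of the intervention:** "After providing informed consent, participants in both the intervention group and control group will engage in a tablet-based survey". After that, "Participants in the control group receive conventional TAU, while participants in the intervention group receive a structured multidisciplinary intervention".
- **Plans to promote participant retention and complete follow-up {18b}:** "Participation in the intervention requires attending a counseling session with a member of the psychosocial team". Later sessions are optional. No equivalent entry step is given for usual care.
- **Implementation {16c} and Trial status:** the allocation was "communicated to all participating pediatric university clinics in March 2023", and "The recruitment started on 1 July 2023".
- **Who will be blinded {17a}:** "blinding of the patients and their parents is not possible".

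**The concern.** Whether a family starts is settled after the clinic has been randomised and after consent and baseline. It can depend on the family's motivation and sense of competence, which lie close to the primary outcome, self-efficacy. If consented families who never start are dropped from intervention clinics, while control families have nothing they could fail to start, the arms are no longer selected in the same way.

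Two things are at stake. The first is the primary estimate, because a selected group in one arm is compared with a less selected or unselected group in the other. The second is the permutation test. Its validity rests on clinic summaries being exchangeable between arms when there is no effect, and a summary over starters is not in general exchangeable with a summary over all families. The same p-value opens the gate to every secondary endpoint. The planned ITT analysis may reveal a discrepancy, but it does not repair the confirmatory test.

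**Working it through.** **No figure in the plan to reproduce.** The article gives no share of non-starters and no outcome gap, so both are assumptions here.

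**Size of the bias.** Let p be the share of intervention-arm families who do not start, and g the mean adjusted outcome of starters minus that of non-starters, in SD units. Suppose there is no treatment effect, the arms are otherwise alike, and no control family is removed. The mean over all families is then μ = (1 − p)·μ_start + p·μ_non, so μ_start = μ + p·g. The control mean is μ, and the difference between arms is p·g.

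| p | g = 0.1 | g = 0.3 | g = 0.5 |
|---|---|---|---|
| 0% | 0 | 0 | 0 |
| 5% | 0.005 | 0.015 | 0.025 |
| 10% | 0.01 | 0.03 | 0.05 |
| 20% | 0.02 | 0.06 | 0.10 |
| 30% | 0.03 | 0.09 | 0.15 |

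With g = 0 the bias is nil whatever p is. The largest entry, 0.15 SD, is 0.15/0.3 = 50% of the planned effect. If g is negative, the sign reverses and the bias works against the intervention.

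**Standard error.** Inputs from Sample size {14} are an intra-cluster correlation of 0.022 and 10% loss to follow-up. Sequence generation {16a} gives five clinics per arm. The article has two totals: at least 160 participants overall in Sample size {14}, and 160 expected per clinic, hence 1,600, in Recruitment {15}. Both are carried forward, with equal cluster sizes assumed.

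- 1,600 participants: 160 × 0.9 = 144 per clinic; design effect 1 + 143 × 0.022 = 4.15; effective n per arm 5 × 144/4.15 ≈ 174; SE = √(2/174) ≈ 0.107 SD.
- 160 participants: 16 × 0.9 = 14.4 per clinic; design effect 1 + 13.4 × 0.022 = 1.29; effective n per arm 5 × 14.4/1.29 ≈ 56; SE = √(2/56) ≈ 0.19 SD.

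**Rejection rate with no true effect.** The reference is the noncentral t with 10 − 2 = 8 degrees of freedom and noncentrality bias/SE. The test is assumed two-sided at 5%, since the article does not state sidedness. The t test stands in for the permutation test.

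| Bias (SD) | 1,600 participants | 160 participants |
|---|---|---|
| 0 | 5.0% | 5.0% |
| 0.02 | 5.3% | 5.1% |
| 0.05 | 7.0% | 5.6% |
| 0.10 | 13.1% | 7.5% |
| 0.15 | 23.5% | 10.8% |

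A normal approximation would give 15.4% at 0.10 SD with 1,600 participants. With only ten clinics, the t figure is the better guide.

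**The case against.** The article does not say that starting means attending counselling, or that the filter applies to one arm only. It uses the word intervention for both arms in Implementation {16c}, in the section on discontinuing allocated interventions {11b}, and in the subgroup definition in {20b}. Starting could therefore mean starting the allocated care. The intervention also has a medical component. Consent and baseline take place in the waiting time before the appointment, so a family that goes on to that appointment has arguably started. Non-starters could then be very few. The counselling requirement stands in a section on retention, not in a definition of an analysis set, and details are deferred to an analysis plan that is not shown.

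Much of this stands as a limit on the claim. A reader might infer that the filter certainly removes only intervention families; that is a well-supported inference, not a stated rule. None of the alternatives gives a rule that is clearly comparable between arms, however. Taken literally, the definition excludes every control family. Taken as allocated care, it is nearly empty under usual care but could still remove intervention families. If it meant only attending the appointment, the set would nearly coincide with ITT, yet the article lists the two separately. Deferring details does not help either, because the article itself fixes the set.

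A reader might also infer that the bias must favour the intervention. The document does not support this. The endpoint is improvement, the test adjusts for subject-level covariates, and self-efficacy is measured at baseline, so a stable difference in level may largely drop out. The number of contacts follows need, so families who already feel capable may be the ones who decline.

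**Conclusion.** The point holds in a limited form. The confirmatory test, and the gate to the secondary endpoints, rest on a set defined by a post-randomisation event that has no stated equivalent under usual care. This can bias the comparison; whether it does, and in which direction, cannot be determined from the document.

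The range of 0 to 0.15 SD rests on the assumed 0–30% non-starters, the assumed gap of 0–0.5 SD, and removal from the intervention arm only. The inflation of type I error also depends on which total applies and is negligible at the lower end of the range.

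It would be tempting to call the ITT comparison unbiased. The document does not support that: clinics knew their allocation about three months before recruitment began, and families consented at clinics that knew it, so consent itself may be selective. ITT removes the filter applied after consent, and nothing more.

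**What to change.** Define the primary analysis set, for the primary and secondary endpoints, as all consented participants with a baseline (T0) assessment. Analyse them by their clinic's allocation whether or not they attended any session, with the multiple imputation already planned for missing follow-up values. Keep the set of starters as a sensitivity analysis, and state for each arm which event counts as starting.

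The cost is wording in the protocol and the analysis plan. ITT is already planned, so in effect the two sets exchange roles.

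The downside is a possibly smaller estimate. For illustration, if the effect were 0.3 SD in starters and zero in non-starters, the ITT effect would be 0.3 × 0.9 = 0.27 SD with 10% non-starters and 0.3 × 0.7 = 0.21 SD with 30%. With 1,600 participants, equal clusters and t on 8 degrees of freedom, power would fall from about 69% to about 60% and 41%.

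Possible selection at consent remains and should be examined separately, for example with the data on families who decline that the article already plans to collect.
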